### Secondary outcome measures

(i) Treatment effects: at three months and one year, the treating physician will be asked to reassess the HF etiology. The presence of each HF medication class will be re-assessed in addition to the overall number of cardiac medications. The presence of advanced HF therapies will additionally be recorded at each follow-up visit including: implantable device, electrophysiologic study/ablation, cardiac surgery/transplantation, and disease specific therapies (for example, phlebotomy for hemochromatosis; steroids for sarcoidosis).

(ii) Clinical endpoints: Composite Clinical Endpoints (CCE that is, death, cardiovascular (CV) death, HF admission), left ventricular function, QoL, referral to HF clinic, costs and safety will be assessed at three months, then annually for a minimum of one year and a maximum of four years.

Resource utilization and costs: regression methods will be used to assess the incremental costs associated with the routine use of CMR.

(iii) Echo/CMR variability: anonymized copies of CMR and echo studies will be sent to a core lab for interpretation in approximately 10% of cases in order to assess reproducibility and quality assurance of the results. Appendix A.

### Statistical analysis

Descriptive statistics will be used to summarize the characteristics of the patients for each imaging technology on demographic, clinical and site related factors, and differences between these groups will be reviewed for their clinical significance.

#### Analysis populations

For the purposes of data analysis, three study populations will be considered: Intent-to-treat (ITT) population, As-treated population and Per-protocol population. The ITT population will be used for the main analysis for all primary and secondary objectives, except for the safety analysis where the As-treated population will be used. As a secondary analysis, the analyses will be repeated for the As-treated and Per-protocol populations.

#### Primary analysis

For the primary analysis, the definitive diagnosis of cardiomyopathy between routine CMR versus echo with selective CMR, diagnosis will be compared using chi-square techniques. Potential confounding variables of the relationship between the imaging strategies and the primary endpoint will be assessed. In particular, propensity scores based on patient factors (for example, in/outpatient, NYHA class, HF duration, diabetes, atrial fibrillation) and site factors (for example, time-to-imaging, time-to-therapy) will be used in the analysis if necessary to adjust for potential differences. A logistic regression model will be used to assess the occurrence of the endpoints between the imaging strategies (model will include a group indicator variable) adjusting for any pertinent baseline differences identified.

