**Figure 1 F1:**
[figure not shown]
**Flow diagram for OUTSMART-HF.** Abbreviations: HF = heart failure and CMR = cardiac magnetic resonance.

Tertiary care sites (in Canada and Finland) with dedicated HF programs will participate in the study (Additional file 1). Consecutive patients will be enrolled at sites with CMR programs (defined as a minimum 200 cases/year) and randomized to routine CMR or selective CMR. Non-ischemic HF patients from sites with smaller CMR programs will be included in a registry of patients undergoing routine HF care (that is, selective use of CMR). All sites will receive approval from local ethics committees (UOHI REB protocol # 2010422-01H) and patients will give written informed consent. Participants in the selective CMR arm may only undergo CMR when there is a suspicion or uncertainty for a diagnosis of: 1) infiltrative cardiomyopathy, 2) arrhythmogenic right ventricular cardiomyopathy, 3) adult congenital heart disease or 4) pericardial disease following standard HF care including echocardiography [35]. Other tertiary sites may be added in year two to three depending on recruitment needs and registry sites may become randomization sites if the experience and wait-time criteria are met.

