#### CMR

Following all HF investigations (including echocardiography), study participants randomized to routine CMR as well as those requiring selective CMR will undergo a conventional scan. The CMR protocol must include an assessment of biventricular volumes and systolic function, LV mass, LA volume (biplane formula), global and regional myocardial edema using T2 weighted sequences, and hyperemia and regional myocardial fibrosis using contrast enhanced T1 weighted sequences. Appendix A. CMR interpreters participating in this trial should report a minimum of 100 cases/year. Local CMR interpreters at each participating center will be expected to complete a standardized clinical report form. The most likely HF etiology based upon the CMR will be provided to the referring physician. All CMR data acquisition and reporting will conform to current published guidelines [41,42].

The echo and CMR reports will be integrated with the other clinical data when used by the treating physician to make a final clinical determination on the HF etiology.

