### Limitations

Given that CMR provides insight into myocardial characterization, we expect that the etiology of heart failure will be better characterized in those HF patients undergoing routine CMR. However, in some instances additional investigations such as myocardial biopsy and invasive hemodynamics may be required to confirm CMR findings. Therefore, the final diagnosis of heart failure etiology may ultimately be determined by CMR driven ancillary testing. We will assess the impact of downstream resource utilization on diagnosis and outcome in the multivariable analysis as well as calculate the additional cost burden.

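### The primary analysis allows a propensity-score adjustment that names time-to-imaging and time-to-therapy; if these are patient-level times they follow randomisation, and the adjusted effect can be biased or less precise

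*Protocol article*

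**What the plan says.** All of the following is in the protocol article.

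- **Allocation** (Design, text after Figure 1): "Consecutive patients will be enrolled at sites with CMR programs (defined as a minimum 200 cases/year) and randomized to routine CMR or selective CMR". In the control arm, "Participants in the selective CMR arm may only undergo CMR when there is a suspicion or uncertainty for a diagnosis of" one of four listed conditions.
- **Imaging** (CMR section): once the other investigations are done, "study participants randomized to routine CMR as well as those requiring selective CMR will undergo a conventional scan".
- **Endpoint** (Primary outcome measure): the treating physician assigns the diagnosis after baseline imaging is complete.
- **Primary test** (Primary analysis): "diagnosis will be compared using chi-square techniques". The Analysis populations section makes intention-to-treat the main population.
- **Adjustment** (Primary analysis): "Potential confounding variables of the relationship between the imaging strategies and the primary endpoint will be assessed". The propensity scores draw on five patient-level examples (atrial fibrillation, diabetes, duration of HF, NYHA class and in/outpatient status). The same sentence goes on to say that "site factors (for example, time-to-imaging, time-to-therapy) will be used in the analysis if necessary to adjust for potential differences".
- **Logistic model** (Primary analysis): it includes the group indicator, "adjusting for any pertinent baseline differences identified".
- **Limitations**: "We will assess the impact of downstream resource utilization on diagnosis and outcome in the multivariable analysis".

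**The concern.** In a randomised comparison, baseline characteristics differ between arms only by chance. A propensity score is not needed to remove confounding, but it does no harm if it contains only variables fixed before randomisation. The difficulty is that the protocol names two variables that may not be of that kind.

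The arm decides who has CMR, so a patient's time to imaging can be a consequence of allocation, and a control patient without CMR has no CMR time at all. Time to therapy is exposed in two ways. The Secondary hypotheses expect routine CMR to change treatment decisions, and therapy may wait for the diagnosis, which is itself the endpoint. Conditioning on such variables can remove part of the effect, or create one through the endpoint. At stake is whether an adjusted estimate reported beside the chi-square result still describes the effect of routine versus selective CMR.

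**Working it through.** **1. The plan's own figure.** Inputs from Sample size justification: 35% vs 50%, alpha 0.05 (taken as two-sided), power 90%, pooled Z-test, 10% loss.

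n = [1.960·√(2·0.425·0.575) + 1.282·√(0.35·0.65 + 0.50·0.50)]² / 0.15² = (1.370 + 0.886)² / 0.0225 ≈ 226.2, so 227 per group.

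Inflation: 226.2/0.90 = 251.3, so 252 (253 if 227 is inflated). The stated 252 reproduces. It rests on the unadjusted comparison and uses no covariate.

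**2. Order of events.** Randomisation, then CMR as the arm dictates, then the physician's diagnosis, with treatment decisions expected to respond to imaging. Patient-level time-to-imaging and time-to-therapy therefore fall after randomisation.

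**3. Precision (assumed inputs).** Let the time have unit SD within arm and a mean shift of s SD between equal arms, unrelated to the outcome. There is no bias, but the variance of the arm effect is inflated by about 1 + s²/4, and power is Φ(3.242/√(1 + s²/4) − 1.960).

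| s | Variance inflation | Power, formula | Power, simulation (226 per arm) |
|---|---|---|---|
| 1 | 1.25 | 0.83 | 0.83 |
| 1.5 | 1.56 | 0.74 | 0.76 |
| 2 | 2.00 | 0.63 | 0.59 |

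Without the time in the model, power is about 0.90.

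**4. Bias when the time depends on the diagnosis (assumed inputs).** Let the time be normal with unit SD and mean s·(arm) + d·(diagnosis). By Bayes' rule the log odds ratio for arm, given the time, is ln(OR) − d·s. The planned OR is (0.50/0.50)/(0.35/0.65) = 1.857. With s = 1:

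- d = −0.5: 1.857·e^0.5 = 3.06 (simulated 3.04; weighted risk difference about 0.25).
- d = +0.5: 1.857·e^−0.5 = 1.13 (simulated 1.13; weighted risk difference about 0.03).

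The true difference is about 0.15 in both. In this model, if s = 0 or d = 0 the odds ratio is unchanged.

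**5. Bias when the time and the diagnosis share a cause (assumed inputs).** At s = 1, the simulated weighted risk difference falls from 0.142 to 0.111 (log odds ratio 0.5 per SD of the shared cause) and from 0.127 to 0.037 (log odds ratio 1.0).

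**6. Time as a marker of being scanned (assumed inputs).** Suppose 95% of routine and 20% of selective patients are scanned, with a specific diagnosis in 51% of scanned and 31% of unscanned patients. The arm rates are 0.95·0.51 + 0.05·0.31 = 0.50 and 0.20·0.51 + 0.80·0.31 = 0.35, as planned. If a scan adds 4 weeks, the simulated adjusted odds ratio (252 per arm, 300 trials) is about 1.07, 1.55, 1.76 and 1.86 when the SD of the time is 0.5, 2, 4 and 8 weeks. The rejection rate runs from about 3% to 91%. The answer turns on a spread that the documents do not give.

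**7. Site-level reading.** A site's usual waiting time, fixed beforehand, is the same for both arms at that site. It has no systematic shift between arms (s = 0), so adjusting for it does not bias the comparison, and confounding gives no reason to do so.

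**The case against.** The best defence is that the text calls the two times site factors and sets them against patient factors. The Design section also treats waiting time as a criterion that a site must meet before it may randomise, and the Discussion refers to differences in MRI access. On that reading nothing post-randomisation enters. This stands as a possible reading, but the text gives neither a definition nor a start point, and time-to-therapy is more naturally a patient event. The harmless reading also leaves the adjustment without a confounding rationale.

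The defence is right on three further points, each of which a reader might be tempted to overstate.

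- One might infer that the primary result is biased. It is not: the unadjusted intention-to-treat chi-square comes ahead of any adjustment, which applies only if judged necessary.
- One might infer that the two times also enter the logistic model. That sentence is limited to baseline differences and names neither. Covariate lists are often left to the statistical analysis plan, which is not at hand.
- One might infer from Limitations that the arm effect will be adjusted for downstream resource use. The text says only that the impact of such use will be assessed, which may be exploratory.

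**Conclusion.** The point holds as a possible flaw in a conditional, adjusted analysis. The protocol names two undefined times as propensity-score variables. On the patient-level reading they follow randomisation, and adjusting for them can bias the effect or widen its interval. On the site-level reading they are not confounders. Neither reading justifies the sentence as written.

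Bias requires that the arm shifts the time and that the time is linked to the diagnosis. A shift alone costs only precision: at 1 SD, power of about 0.83 instead of 0.90. A reader might want a single figure for the bias, or to call the time nearly collinear with the arm. The documents support neither, because they give no waiting times, no spread and no scanning rates by arm. The illustrations move the estimate in both directions and range from negligible to severe. The 252 per group and the primary test stand.

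**What to change.** 1. State that the unadjusted intention-to-treat chi-square is the primary result and that adjusted analyses are supportive.
2. Delete time-to-imaging and time-to-therapy from any efficacy adjustment, or define them as site characteristics fixed before randomisation.
3. Limit the supportive logistic model to pre-randomisation covariates named in advance and included whatever imbalance is observed. In/outpatient status, NYHA class, HF duration, diabetes and atrial fibrillation are already in the text and would serve. If the statistical analysis plan holds such a list, refer to it.
4. Say that downstream testing will be reported by arm as an outcome, and will not be a covariate in the model that estimates the arm effect.

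The cost is a change of wording. No new data are needed, and the sample size and the planned 90% power do not change.

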#### Secondary outcomes

For the binary secondary outcomes, such as CCE, referral to HF clinic and HF therapies, chi-square tests will be used to compare the imaging strategies. Logistic regression analysis will be used for adjusting any pertinent baseline differences identified. For continuous secondary outcomes, such as LV function, MLHFQ and EQ5D, analysis of variance will be used to compare trends over time between the imaging strategies. Analysis of covariance will be used for adjusting any pertinent baseline differences identified. For assessing the reproducibility of echo/CMR results, reliability statistics, including intra-class correlations and kappas, will be calculated to compare CMR and echo studies with the core lab interpretations.

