#### Secondary hypotheses

Routine use of CMR will have a significant impact on treatment decisions, and will (1) lead to more disease specific therapies and/or (2) cause a significant change in the number and class of HF medications, during follow-up. The routine CMR group will also have improved clinical outcomes (CCE), symptoms and QoL and decreased costs compared to the standard of care group during follow-up.

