### Study population

We will recruit patients with either newly diagnosed HF within the past 12 months or established HF patients with deterioration/decompensation within the past 12 months.

*Inclusion criteria:*

Patients with new or worsening HF as above *and*:

1) age > 18 years

2) working clinical diagnosis (known or highly suspected) of non-ischemic cardiomyopathy (NICM) or clinical diagnosis of HFPEF (signs or symptoms of heart failure with a LVEF ≥ 40%)

3) documented history of Class II-IV NYHA HF symptoms within the past 12 months

*Exclusion criteria:*

1) prior CMR and no major change in clinical condition

2) well-documented specific etiology (for example, known amyloidosis or hemochromatosis)

3) physician considers cause of heart failure is attributable to obstructive CAD

4) documented previous ST-segment elevation myocardial infarction (STEMI) (any territory) or non-ST-segment elevation myocardial infarction (NSTEMI) in the left anterior descending coronary artery territory

5) evidence of multi-vessel ischemia on stress imaging

6) ongoing need for advanced heart failure support (for example, inotropes or intra-aortic balloon pump)

7) severe valvular heart disease requiring surgery within the next six months

8) contraindications to CMR (for example, certain metallic implants, severe claustrophobia)

9) contraindications to gadolinium contrast agent (glomerular filtration rate < 30 ml/min/1.72 m^2^, pregnancy)

10) severe medical conditions that significantly affect the patient's outcome (for example, active malignancy)

11) inability to give informed consent

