#### Sample size justification

Based on a study of patients with NICM (prior to availability of CMR) a myocardial biopsy adds a specific diagnosis to standard approaches in 15% of patients with NICM increasing the rate from 35% to 50% [7]. For the sample size determination, the estimated occurrence of a definitive diagnosis with CMR is 50% and echo (with selective use of CMR) is 35%. For the primary analysis comparing routine CMR versus selective CMR with a sample size of 252 per group is required to detect a difference in the event rate of definitive diagnosis of cardiomyopathy of 35% (selective CMR) versus 50% (routine CMR), based on the Z-test with a pooled variance estimate, and after adjustment for 10% patient loss or withdrawal, we will be able to detect a difference in the event rate of definitive diagnosis of cardiomyopathy of 35% (selective CMR) versus 50% (routine CMR), a level of significance of 0.05, power of 90% and an adjustment for 10% patient loss or withdrawal.

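### The test for HF medication classes uses baseline use of the same class only if an imbalance is noticed, although the hypothesis is about change: a cost in precision and fit, not in validity

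*Protocol article*

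**What the plan says.** All places are in the Protocol article.

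- **Secondary hypotheses.** Routine CMR is expected to "lead to more disease specific therapies" and/or "cause a significant change in the number and class of HF medications, during follow-up".
- **Secondary outcome measures, item (i).** At three months and one year, "The presence of each HF medication class will be re-assessed in addition to the overall number of cardiac medications". Advanced and disease-specific therapies are recorded separately at each follow-up visit.
- **Statistical analysis, Secondary outcomes.** The test is named here: "For the binary secondary outcomes, such as CCE, referral to HF clinic and HF therapies, chi-square tests will be used to compare the imaging strategies". The next sentence adds: "Logistic regression analysis will be used for adjusting any pertinent baseline differences identified".
- **Study population.** Besides newly diagnosed patients, the trial enrols "established HF patients with deterioration/decompensation within the past 12 months". Patients whose specific etiology is already well documented are excluded.
- **Description of interventions.** Baseline clinical data are collected on every participant.

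The article states no therapy rates at entry, no start or continuation rates, and no power for this outcome.

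**The concern.** The hypothesis is about change, the recorded variable is presence, and the named test compares presence between arms. A patient who was on a class before randomisation and stays on it counts as a yes at follow-up, although the imaging strategy had no part in it. In a trial that includes established heart failure, such patients may be a large share of the yes count.

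The regression clause does not remove this, because observed imbalance triggers it. Entry use matters because it predicts the outcome, whether or not the arms happen to differ on it. With balanced arms the clause need not fire, and what is probably the strongest predictor goes unused.

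The therapy outcome links a better diagnosis to altered care, and the Discussion lists it among the design's attractions. A real shift in prescribing could be reported as no effect.

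**Working it through.** **1. The plan's own figure.** Sample size justification: 35% vs 50%, alpha 0.05 (taken as two-sided), power 90%, pooled Z-test, 10% loss.

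n = [1.960 × √(2 × 0.425 × 0.575) + 1.282 × √(0.35 × 0.65 + 0.50 × 0.50)]² / 0.15² = 226.2 per arm; 226.2 / 0.9 = 251.3, so 252.

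The stated 252 reproduces. It belongs to the primary outcome. Evaluable per arm: 252 × 0.9 = 226.8, taken as 227.

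**2. Assumed inputs (none is in the article).** b = proportion on the class at entry; s = proportion of those still on it at follow-up, equal in both arms; p0 and p1 = start rates among non-users in the selective and routine arms.

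**3. Formulas.** Follow-up prevalence in arm j is Pj = b·s + (1 − b)·pj, and the arm difference is d = (1 − b)(p1 − p0). For both tests, power = Φ{[d√227 − 1.96√V0] / √V1}.

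- Chi-square: V0 = 2P̄(1 − P̄); V1 = P0(1 − P0) + P1(1 − P1).
- Stratified by entry use: V0 = 2[b·s(1 − s) + (1 − b)p̄(1 − p̄)]; V1 = 2b·s(1 − s) + (1 − b)[p0(1 − p0) + p1(1 − p1)].

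**4. One case in full.** b = 0.30, s = 0.90, starts 20% vs 35%.

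- P0 = 0.27 + 0.14 = 0.41; P1 = 0.27 + 0.245 = 0.515; d = 0.105; d√227 = 1.582.
- Chi-square: √V0 = 0.705, √V1 = 0.701; (1.582 − 1.382) / 0.701 = 0.285; power 61%.
- Stratified: √V0 = 0.577, √V1 = 0.570; (1.582 − 1.131) / 0.570 = 0.790; power 79%.

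Simulated logistic regression adjusted for entry use agrees: 62% vs 79%.

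**5. Stable therapy (s = 0.90): power by chi-square → with adjustment.**

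| Starts | b = 0.2 | b = 0.3 | b = 0.4 | b = 0.5 |
|---|---|---|---|---|
| 10% vs 20% | 46 → 69 | 34 → 59 | 25 → 48 | 19 → 36 |
| 20% vs 35% | 74 → 86 | 61 → 79 | 48 → 68 | 37 → 56 |
| 35% vs 50% | 73 → 79 | 62 → 71 | 50 → 61 | 39 → 50 |

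Before rounding, the gains run from about 7 to 25 points.

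**6. Where the gain is small.**

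- Continuation 70%, b = 0.3, starts 35% vs 50%: 62% vs 63%.
- Continuation 70%, b = 0.4, starts 35% vs 55%: 74% vs 76%.
- b = 0.1, s = 0.90, starts 35% vs 50%: about 2 to 3 points.
- b = 0.8, s = 0.90, starts 35% vs 55%: about 4 points.

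Over a wider grid (b 0.1 to 0.8, s 0.8 to 1.0) the gain runs from about 1 to 39 points. Low entry use does not guarantee a small gain: at b = 0.1 with starts 10% vs 20%, the formulas give 63% vs 78%. At b = 0 the two tests coincide.

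**7. Validity.** With no arm difference, the chi-square rejected in 5.2% to 5.3% of 20,000 simulated trials in each of three settings.

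**8. Offsetting changes.** Take b = 0.5, continuation 90% vs 75%, starts 20% vs 35%. Follow-up prevalence is 0.45 + 0.10 = 0.55 and 0.375 + 0.175 = 0.55, so there is no difference in presence. Any change from entry is 0.05 + 0.10 = 0.15 vs 0.125 + 0.175 = 0.30. Simulated power is 5% for the chi-square on presence, 5% with adjustment for entry use, and 97% for a chi-square on any change.

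**The case against.** The strongest reply is that the tested variable is inferred. The Secondary outcomes paragraph says only HF therapies, and a fuller protocol or SAP, not shown here, could code the outcome as a start or a change. The named chi-square would then lose little. In four simulated cases (entry use 30% to 50%, continuation 85% to 90%), power was:

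| | Case 1 | Case 2 | Case 3 | Case 4 |
|---|---|---|---|---|
| Chi-square on presence | 61% | 58% | 59% | 63% |
| Stratified by entry use | 69% | 71% | 79% | 83% |
| Chi-square on new start | 73% | 81% | 86% | 87% |
| Chi-square on any change | 64% | 69% | 77% | 82% |

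That reading is possible, but it is not what the article says: the outcome section describes presence, re-assessed. The article also fixes a test and a trigger for adjustment, so this is a stated choice and not a detail left out.

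Three parts of the reply stand. The rates are all assumed. The test is valid. Adjustment alone does not answer a hypothesis about change, because offsetting starts and stops stay hidden (step 8 of the working).

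A reader might go further and infer a fixed loss, such as the 8 to 20 points between the first two rows. The documents do not support that: those cases assume high continuation and an effect on starts only. Nor do they support calling the analysis biased, or saying that adjustment is absent; it is conditional.

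**Conclusion.** The point holds for the HF medication classes as a matter of precision and fit to the hypothesis. As written, entry use of the same class is ignored whenever the arms look balanced, and presence is compared where the hypothesis speaks of change.

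Under assumed rates with 227 per arm, always adjusting typically gains about 7 to 25 points of power when therapy is stable. The gain can fall to about 1 to 4 points when continuation is low or entry use is very low or very high. Whether 'typical' applies depends on rates that the article does not give.

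For disease-specific therapies the loss should be small, so far as excluding known specific etiologies leaves hardly anyone on them at entry. The primary analysis and its sample size are unaffected. The change is worth making because it is nearly free.

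**What to change.** In Statistical analysis, Secondary outcomes:

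- For each HF medication class at three months and one year, prespecify a logistic regression on randomised arm and presence of that class at entry, or a Mantel-Haenszel test stratified by entry use. Fit it whether or not an imbalance is seen.
- Report an adjusted risk difference beside the odds ratio, and keep the chi-square as a supporting analysis.
- Because the hypothesis is about change, also compare between arms the proportion whose class status differs from entry. Show starts among non-users and stops among users separately.

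The cost is wording only. The outcome is described as re-assessed and baseline clinical data are collected on all participants, so the entry value appears to be held already; this should be confirmed on the case report form. One small drawback is that the odds ratio becomes conditional on entry use, which is why the risk difference should accompany it.

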**Design:**

Tertiary care sites in Canada and Finland, with dedicated HF and CMR programs, will randomize consecutive patients with new or deteriorating HF to routine CMR or selective CMR. All patients will undergo a standard clinical echocardiogram and the interpreter will assign the most likely HF etiology. Those undergoing CMR will also have a standard examination and will be assigned a HF etiology based upon the findings. The treating physician’s impression about non-ischemic HF etiology will be collected following all baseline testing (including echo ± CMR). Patients will be followed annually for 4 years to ascertain clinical outcomes, quality of life and cost. The expected outcome is that the routine CMR arm will have a significantly higher rate of infiltrative, inflammatory, hypertrophic, ischemic and ‘other’ cardiomyopathy than the selective CMR group.

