### Follow-up

Clinical outcomes will be collected by telephone follow-up, and/or by hospital chart and electronic health record review at three and twelve months and then yearly up to four years, following completion of baseline scans. Data will be recorded on standardized case report forms. Quality of life questionnaires (MLHFQ and EQ5D) will be administered at each follow-up.

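### The composite clinical endpoint is tested by chi-square with no time point although follow-up runs from one to four years; a time-to-event analysis fits the design better

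*Protocol article*

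**What the plan says.** In the protocol article, the Secondary outcomes paragraph under Statistical analysis reads: "For the binary secondary outcomes, such as CCE, referral to HF clinic and HF therapies, chi-square tests will be used". Adjustment follows the same binary form: "Logistic regression analysis will be used for adjusting any pertinent baseline differences identified". Neither sentence names a visit or horizon for the CCE.

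The Secondary outcome measures section defines the endpoint as "Composite Clinical Endpoints (CCE that is, death, cardiovascular (CV) death, HF admission" and has it "assessed at three months, then annually for a minimum of one year and a maximum of four years". The Follow-up section collects outcomes "at three and twelve months and then yearly up to four years, following completion of baseline scans". The abstract's Design paragraph instead says: "Patients will be followed annually for 4 years to ascertain clinical outcomes, quality of life and cost".

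The Missing data paragraph assumes data are missing at random and names multiple imputation, with a repeated-measures model for continuous outcomes. It does not mention patients whose observation ends because the study closes. The Secondary hypotheses section expects better CCE results in the routine CMR arm. The Study management section has every clinical event adjudicated by a committee blinded to allocation.

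**The concern.** Death and HF admission happen at a time, and under the stated schedule patients are watched for different lengths of time. A yes/no comparison with no horizon treats a patient event-free at one year like a patient event-free at four. The resulting proportion depends on how recruitment was spread over the calendar, so it cannot be read as a one-year, a four-year or any other risk. An early event also counts the same as a late one.

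At stake are the interpretation and efficiency of the comparison behind the hypothesis of improved clinical outcomes, which the Discussion presents as one of the trial's attractions. This is a method that the article states, not a detail left for an analysis plan.

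**Working it through.** **Inputs from the article.** 252 patients per arm; follow-up from one to four years; CCE tested as a binary outcome. The article states no CCE rate, treatment effect or accrual pattern.

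**The article's own figure.** Only the primary endpoint has a sample size calculation. With 35% vs 50%, two-sided alpha 0.05 (sidedness is not stated), power 90% and pooled variance:

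n = [1.96·√(2·0.425·0.575) + 1.2816·√(0.35·0.65 + 0.50·0.50)]² / 0.15² = (1.370 + 0.886)² / 0.0225 ≈ 226.2, so 227 per arm.

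227 / 0.90 = 252.2, which agrees with the stated 252. That figure is sound and serves below as the arm size.

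**What the ever/never proportion measures.** Assume a constant hazard λ = −ln(1 − r) for yearly risk r, and follow-up uniform on 1 to 4 years. Risk by year k is 1 − (1 − r)^k. The pooled proportion is 1 − (e^(−λ) − e^(−4λ)) / (3λ). For r = 20%: λ = 0.223, and 1 − (0.800 − 0.4096) / 0.669 = 42%.

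| Assumed yearly risk | By 1 year | By 4 years | Pooled over 1–4 years |
|---|---|---|---|
| 10% | 10% | 34% | 23% |
| 20% | 20% | 59% | 42% |
| 30% | 30% | 76% | 57% |

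The last column moves between the two before it with the accrual pattern alone.

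**Power.** Simulated trials with 252 per arm, exponential event times, follow-up uniform on 1 to 4 years, hazard ratio 0.70 and no loss. Ranges are repeat runs.

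| Control rate (assumed) | Chi-square, ever/never | Log-rank | Chi-square at 12 months |
|---|---|---|---|
| 10% per year | 41% | 42% | 22% |
| 20% per year | 64% | 67% | 39% |
| 30% per year | 76% | 81% | 52% |
| hazard 0.25 per year | 67–69% | 71–73% | 42–43% |
| hazard 0.40 per year | 78–80% | 83–85% | 57–58% |

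At hazards of 0.25 to 0.40, ever/never costs about 3 to 5 points against log-rank, and the 12-month test about 25 to 30. At 10% per year the gaps are about 1 and 20 points.

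**Type I error (hazard ratio 1).**
- Same follow-up distribution in both arms, no loss: chi-square 4.9%, 5.2% and 6.0% at 10, 20 and 30% per year. Log-rank is also near 5%.
- Equal loss of 5% per year in both arms: still close to 5% for both tests.
- Unequal loss, with lost patients coded event-free, hazard 0.25 per year: about 8% for yearly loss of 6% vs 2%, and about 16–17% for 12% vs 3%.
- One arm observed three months less, no loss: about 13%.

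Log-rank stays near 5% in the unequal scenarios because simulated drop-out is independent of prognosis.

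**How large those losses are.** With a yearly loss hazard d, the share lost before the planned end is 1 − (e^(−d) − e^(−4d)) / (3d). For d = 0.12 and 0.03 this is 26% and 7%, about 16% overall. For 0.06 and 0.02 it is 14% and 5%, close to 10% overall. The article's only loss figure is 10%, given for the primary endpoint. With 14% vs 5% lost, the chi-square error runs from 5.6% to 9.2% over hazards of 0.10 to 0.40.

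**The case against.** A reader might infer that this test makes the CCE result invalid: that patients lost early are counted as event-free, so unequal loss between open-label arms becomes a false difference. The documents do not support that.

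- No such coding is stated, and the Missing data paragraph names multiple imputation.
- Nothing in the article shows unequal loss. Outcomes may be taken from hospital charts and electronic records, which limits loss for deaths and admissions.
- Randomisation should balance administrative follow-up. The 16–17% figure needs both a steep assumed imbalance and the unstated coding.
- Log-rank is no guarantee either: if drop-out is related to prognosis, it and Cox are biased too.

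A reader might also argue that the routine arm is observed for less time, because follow-up starts when baseline scans are complete and every patient in that arm waits for CMR. The article gives no waiting times and does not say that follow-up closes on a calendar date, so the three-month scenario is an illustration only.

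A valid reading of the chi-square does exist: a comparison at 12 months, which every patient should reach. Its cost is power, not validity. Finally, only a condensed article is shown, so the absence of a time-to-event method is established for the article alone.

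These points remove the claim of demonstrated bias. They do not rescue the stated test: it is tied to no visit, and the imputation sentence does not address administrative censoring.

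**Conclusion.** The concern holds as a mismatch between the stated method and the stated follow-up. The proportion to be compared has no defined horizon, and event timing is lost. The power cost is modest if all follow-up is used and substantial if the test is cut at 12 months. These sizes rest on assumed constant hazards, a hazard ratio of 0.70 and uniform follow-up over one to four years; none of these comes from the article.

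Inflated type I error is conditional: it requires observed follow-up to differ by arm and unobserved time to be treated as event-free. It should not be reported as a property of the plan. Because the CCE is secondary and the primary comparison and sample size are untouched, this should be fixed but does not threaten the trial's main conclusion.

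The abstract's four years against the body's one-to-four is a minor inconsistency, possibly shorthand. It matters here because the length of follow-up decides how poorly the binary analysis fits.

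**What to change.** - Analyse the CCE as time from randomisation to first death or HF admission, censored at last contact. Cardiovascular death is already contained in death. Report Kaplan-Meier curves, a log-rank test and a Cox model.
- Use cumulative-incidence methods for HF admission alone and for cardiovascular death, where other deaths compete.
- Keep chi-square and logistic regression only for a named visit that every patient should reach (3 or 12 months).
- Make the abstract's follow-up length agree with the Follow-up and Secondary outcome measures sections.

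The cost is small: a change of wording, event and last-contact dates on the case report forms, and slightly more analysis work. Events are already adjudicated one by one. The change should be made before outcomes are examined by arm, so that neither method nor horizon is chosen from the data.
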